**Fig. 1 Fig1:**
[figure not shown]
Application points of LLLT

Participants will assume a sitting position and the laser probe will be placed on the knee points sequentially and perpendicularly and in full contact with the skin. All participants will attend the LLLT sessions three times per week over a period of 3 weeks in the combined treatment groups and for 8 weeks when used as monotherapy.

#### Muscle stretching exercises

Before running stretching exercises, patients will hold a 10-min period for warming up on a stationary bike with light load (3/9) and comfortable speed. However, those unable to use this machine will warm-up on a treadmill at a speed of 2.0 km/h and no slope.

The treatment will be conducted in groups of five to seven people at a frequency of 3×/week and lasting approximately 45 min. The intervention will last 8 weeks, completing 24 sessions and will consist of seven segmental stretching exercises, repeated four times and sustained for 30 s each. The intensity will follow the recommendation of the American College of Sports Medicine [35] positioning with middle discomfort. Unilateral exercises are performed alternately, allowing the contralateral limb to rest during execution. For bilateral exercises, a rest period of 30 s between the repetitions will be established. Participants will be correctly positioned and the responsible physiotherapist will guide body awareness, breathing and alignment throughout the therapy. After completing each exercise, individuals will adopt a posture of rest.

The major muscles of the posterior and antero-internal hip muscle chains will be stretched: paraspinal muscle, gluteus, iliopsoas, hamstrings, quadriceps, hip adductors and gastrocnemius (Fig. 2 – Stretching exercises).

**Fig. 2 Muscle stretching exercises Fig2:**
[figure not shown]
ᅟ

#### Control

The control group will receive an educational booklet at the baseline visit consisting of explanations about the disease, postures during daily activities and information for the management of pain. The physiotherapist will explain in detail each item and make weekly telephone follow-up questioning about doubts regarding the educational content and the participants’ state of health. Reassessment will occur after 8 weeks.

### Randomisation and allocation concealment

The randomisation schedule will be prepared by a researcher not involved in participant recruitment, assessment or treatment using a computer-generated random numbers table. There will be a 1:1 allocation ratio of participants to each one of the five groups. Randomisation will be conducted by random permuted blocks of same size. Each group will have 29 numbers. The list containing this information will remain with the physiotherapist responsible for the treatment.

A number will be assigned to participants according to the order of their evaluation. This digit will be later located in the list and, thus, the corresponding group will be identified. The assessor will perform the assessment unaware of the group to which each participant will belong. After the initial evaluation, the participant will be informed by the physiotherapist responsible of the type, time and frequency of treatment.

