**Methods:**

This study will involve 145 people aged 50–75 years with symptomatic-radiographic knee OA. It will consist of two types of treatments: Low-level laser therapy (LLLT) and stretching exercises. The patients will be randomly allocated to five groups LLLT_ACTIVE_+Stretch, LLLT_PLACEBO_+Stretch, Stretch, LLLT and Control (*n* = 29 each). Treatment frequency will be three sessions/week for all active groups. LLLT will involve the use of a Gallium-Arsenide laser (904 nm, 40 milliwatts, 3 J/point, 27 J/knee) over 24 sessions for the monotherapy group and 9 sessions for the LLLT+Stretch groups. Stretching will consist of seven exercises completed over 24 sessions. The control group will receive a booklet. Participants will be treated for 2 months (Stretch, LLLT and Control groups) or 3 months (LLLT + Stretch groups). Participants and the outcome assessor will be blind to treatment allocation throughout the study.

The primary outcome is pain measured by Visual Analogue Scale. Secondary outcomes include quality of life assessed by Western Ontario and McMaster Universities Arthritis Index, function by Lequesne Algofunctional Index, mobility by Timed Up and Go Test, KROM by goniometry of knee flexion and hamstring shortening by popliteal angle. The statistical method will follow the principles of per-protocol analysis.

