### Study procedure

All participants will be screened by an orthopaedist or rheumatologist to diagnose and identify the severity of KOA. The diagnosis will be based on the radiograph analysis and physical assessment and the severity will follow the Kellgren & Lawrence classification. After confirmation of KOA patients will be referred to the local physiotherapy sector. The eligibility criteria will be applied during the prior assessment standardized by the clinic, and when the patient is considered eligible and is interested in participating in the study, their contact (full name and phone number) will be passed to the study assessor in order to schedule the baseline assessment.

Participants will be instructed to bring knee radiographs, prescription medications taken and the referral for physical therapy. Participants will be asked to use comfortable clothes and not to use analgesic or anti-inflammatory drugs 48 h prior the evaluation date, but to continue to perform their ADLs in the usual way. On the baseline visit, the criteria for inclusion and exclusion will be reapplied.

Five intervention groups will be part of the study:LLLT_ACTIVE_ + Stretch: 3 weeks of low intensity laser therapy (LLLT) followed by 8 weeks of stretching exercises.LLLT_PLACEBO_ + Stretch: 3 weeks of placebo LLLT followed by 8 weeks of stretching exercises.Stretch: 8 weeks of stretching exercises.LLLT: 8 weeks of active LLLT.Control: minimal intervention through educational booklet.

This study will be conducted by a trained physiotherapist.

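### Allocation concealment is not secured: the sequential list stays with the treating physiotherapist and no barrier to reading ahead is described

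*Protocol article*

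**What the plan says.** The protocol article, section Randomisation and allocation concealment, describes these steps:

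- A researcher with no part in recruitment, assessment or treatment prepares the schedule from computer-generated random numbers.
- On the ratio: "There will be a 1:1 allocation ratio of participants to each one of the five groups". On the method: "Randomisation will be conducted by random permuted blocks of same size. Each group will have 29 numbers".
- On custody: "The list containing this information will remain with the physiotherapist responsible for the treatment".
- On use: "A number will be assigned to participants according to the order of their evaluation". That number is afterwards found in the list, which gives the group.
- The assessor works without knowing which group the participant will join. After the initial evaluation the treating physiotherapist tells the participant what the treatment is.

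The section Study procedure describes the route into the trial. An orthopaedist or rheumatologist screens, and then "After confirmation of KOA patients will be referred to the local physiotherapy sector". Eligibility is judged at the clinic's routine prior assessment, by a person not named. Contact details of eligible patients go to the study assessor, who schedules the baseline visit, where the criteria are applied again. The section closes by saying that a trained physiotherapist conducts the study.

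The section Statistical analysis compares groups by one-way ANOVA, or Kruskal-Wallis for non-normal data, using the pre-post difference (Average Gain). It names no baseline covariate. The section Timeline says that all participants completed in December 2014 and that analysis was to finish by August 2015.

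**The concern.** Independent generation protects how the sequence is made. Concealment depends on who can see it before each patient is entered. Here the whole sequence goes to a person who works at the site and treats the patients, and list position is fixed by order of evaluation. The text describes a look-up in a list. It mentions no sealed envelope, central release or other step that would stop the holder from knowing the next assignment. This is a stated procedure under a heading that claims concealment, so it is more than a detail lost in condensing.

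If the next assignment can be known, the decision to enter a patient, or the order in which patients come to evaluation, could depend on it. One exclusion criterion (other conditions affecting the ability to take part) calls for judgement. Blinding the assessor does not undo selection that happened before the assessor met the patient. The primary outcome is self-marked pain, and the arms range from 9 + 24 = 33 supervised sessions to a booklet with weekly telephone calls, so a preference about who goes where is plausible. The planned comparison of unadjusted gains offers no protection, because change in pain usually depends on starting pain.

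A second weakness is that a small fixed block size would let someone without the list infer part of the sequence. The arms (laser, group stretching, booklet) are easy to tell apart in a clinic.

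**Working it through.** **Custody and access.** Set side by side, the article's statements are:

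| Step | Who, according to the article | Protects concealment? |
|---|---|---|
| Generating the schedule | Uninvolved researcher | Generation only |
| Holding the list | Treating physiotherapist | No barrier described |
| Taking the next position | Order of evaluation | No; the next position is known in advance |
| Applying eligibility at the clinic | Not stated | Cannot be judged |
| Scheduling and baseline visit | Assessor, stated to be unaware | Yes, for the assessor |

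For the list holder, nothing in the text stands between the list and the next assignment.

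**Inputs for the block size.** Total 145 (Abstract, Methods); five arms at equal allocation, blocks of one size, and "Each group will have 29 numbers" (Randomisation and allocation concealment).

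1. The plan's own total is reproduced: 5 × 29 = 145.
2. A block balanced over five arms must be a multiple of 5. Complete blocks of one size must divide 145. Since 29 is prime, the only multiples of 5 that divide 145 are 5 and 145.
3. Other sizes do not fit: 145/10 = 14.5, 145/15 = 9.67, 145/20 = 7.25 and 145/25 = 5.8 blocks.
4. The article speaks of blocks in the plural, which leaves size 5, in 145/5 = 29 blocks.
5. Check on incomplete blocks: a list in blocks of 10 cut at 145 has 14 full blocks (28 per arm) and half a block. It gives exactly 29 per arm only if that half holds each arm once, with probability 2⁵/C(10,5) = 32/252 = 12.7 %.

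**Predictability with block size 5, past allocations known.** At the five places of a block, the best guess is right with probability 1/5, 1/4, 1/3, 1/2 and 1.

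- Sum = 0.2000 + 0.2500 + 0.3333 + 0.5000 + 1.0000 = 2.2833.
- Mean = 2.2833/5 = 0.457, or 45.7 %.
- Over the trial: 29 × 2.2833 = 66.2 of 145 right, against 145/5 = 29 (20 %) by chance.
- Last places, certain: 29 of 145 (20 %). Fourth places, a choice between two arms: another 29.

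These figures measure how far assignments could be foreseen. They do not estimate bias in the VAS comparison, and the documents give nothing from which that bias could be calculated.

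**The case against.** The strongest reply is that concealment matters for whoever enrols, and the text keeps that person away from the list. A physician screens, the assessor schedules and reapplies the criteria, the assessor is stated to be unaware, and the group is looked up only later. The article does not say that the list lay open, and a full protocol might describe envelopes.

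Much of this stands. A reader might infer that allocation was open, or that the treating physiotherapist steered entry. The documents support neither. Openness would be an inference from the look-up and the missing barrier. No section says that the list holder screens, schedules or enrols, or that the physiotherapist who conducts the study is the one who holds the list. What remains is that the article does say where the list was kept, does not say who applied eligibility in the physiotherapy sector, and still claims concealment.

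A reader might also take 45.7 % as the degree to which this trial was predictable. It needs one person who knows the block size and all past allocations and can also influence entry, and the documents identify no such person. The list holder would not need to guess at all. The block size itself is never given, and 5 rests on complete, balanced blocks.

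On the analysis, it can be said that the Average Gain already uses the baseline value. Subtracting the baseline does not remove the dependence of change on baseline, so adjustment still adds something. It is fair to say that it cannot correct for unmeasured factors.

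**Conclusion.** The point holds in a limited form. As described, the procedure does not secure allocation concealment: the treating physiotherapist keeps the sequential list, positions follow order of evaluation, and no barrier is described. Independent generation and an unaware assessor reduce the risk without closing it. No breach is shown.

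The block size is secondary. Assuming complete and balanced blocks, it is 5. Assuming further that someone knows that size and the past allocations, 29 of 145 assignments are certain and 45.7 % are guessed correctly, against 20 % by chance.

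The size of any resulting bias in pain is unknown. The point deserves correction because the description claims more than the procedure delivers and the planned primary comparison takes no account of baseline imbalance.

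**What to change.** Allocation can no longer be changed in this trial, so the changes concern reporting and analysis:

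1. State who held the list, who could see it before a patient was enrolled, who applied eligibility in the physiotherapy sector, and what block size was used.
2. If a barrier was in fact used, describe it and correct the section. If not, stop describing allocation as concealed and report this as a limitation.
3. Replace the unadjusted one-way ANOVA of pain gain with an ANCOVA on arm, baseline VAS and Kellgren-Lawrence grade. Fix this in writing before the groups are compared, or label it post hoc if they already have been.

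The cost is small. Both covariates are already collected. With all 145 analysed, residual degrees of freedom fall from 145 − 5 = 140 to 137 (one for baseline VAS, two for grades 2 to 4 as categories). The drawback is a change of model after data collection. Adjustment deals only with measured imbalance, so it does not replace the disclosure in items 1 and 2.

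For a future trial only: leave the list with the uninvolved researcher, release one assignment at a time after eligibility and baseline are recorded, and vary the block size without disclosing it.

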### Statistical analysis

All data will be submitted to a descriptive inferential analysis. For adherence to normality, the Kolmogorov-Smirnov test will be conducted. The intergroup comparison will be performed by simple variance analysis (one-way ANOVA) for data with normal distribution and the ANOVA Kruskal-Wallis for non-normal distribution. For statistically significant differences, post hoc tests like Holm-Sidak (parametric) and Tukey test (nonparametric) will be applied. Categorical variables will be compared by chi-square test.

In view of the need to determine clinically important differences, we will calculate the Relative Gain that corresponds to the gain that the patient obtained after the end of treatment relative to how much they could improve. The Average Gain will be calculated for intergroup analysis and will be obtained by the difference between pre and post intervention for each variable. The data will be processed by the software SigmaStat 3.5. The significance level for all analyses will be α = 0.05.

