### Sample size calculation

The primary outcome measure VAS (range: 0–10 cm) was used to estimate the sample size. Using a minimal clinically important change of two-point difference between the treatment groups and control group, with a significance level of 0.05 (2-tailed) and a power of 80 %, we estimated that 25 participants were needed in each group. To allow for a 15 % drop-out rate, we aimed to include 29 participants in each group.

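### After Kruskal-Wallis the article plans a Tukey test; on joint ranks, the power of each two-arm contrast then depends on the other three arms, and pairwise ranking avoids this at almost no cost

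*Protocol article*

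**What the plan says.** The Statistical analysis section of the protocol article chooses between one-way ANOVA and "the ANOVA Kruskal-Wallis for non-normal distribution" according to a Kolmogorov-Smirnov check. If the overall test is significant, "post hoc tests like Holm-Sidak (parametric) and Tukey test (nonparametric) will be applied". It adds that "The significance level for all analyses will be α = 0.05". It does not say whether the ranks are taken over all arms or within each pair.

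The Sample size calculation section works from a "minimal clinically important change of two-point difference between the treatment groups and control group", and "we estimated that 25 participants were needed in each group". No SD is given. On attrition it says: "To allow for a 15 % drop-out rate, we aimed to include 29 participants in each group". The abstract adds: "The statistical method will follow the principles of per-protocol analysis". The Background states the hypothesis that the combination does better than either treatment alone.

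**The concern.** Every pairwise conclusion for an outcome sent to the non-parametric branch comes from this post hoc step, and primary VAS pain could be one of them. A Tukey-type test on joint ranks compares mean ranks across all five arms, with a variance fixed by the total N. If two arms both sit at one end of the scale, patients from the other arms do not fall between them. Their mean ranks are squeezed together, while the critical difference still reflects all five arms.

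This bears on the trial's main question. The Discussion says that the ethics committee did not approve a placebo-laser monotherapy group. The only sham-controlled laser contrast is therefore active v placebo laser, each followed by stretching. If combination treatment works as hypothesised, one or both of these arms lie at the good end. A real difference could then be missed because of data from arms outside the comparison.

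**Working it through.** **1. The plan's own figures.** For a two-sided 0.05 test with 80 % power, n per arm = 2(1.960 + 0.842)² SD² / 2². The SD is not stated, so 25 cannot be reproduced independently. SD 2.0 gives 16, SD 2.5 gives 2 × 7.85 × 6.25 / 4 = 24.5, so 25, and SD 3.0 gives 36. Solving the t-test version for n = 25 gives a standardised difference of 0.809 and SD = 2 / 0.809 = 2.47 cm. An SD of 2.47 to 2.5 cm is therefore assumed below. The 29 follows from 25 × 1.15 = 28.75.

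**2. The joint-rank criterion.** Two arms differ if their mean ranks are further apart than q √(N(N+1)/(12n)), where q = 3.858 for five arms. With n = 25 and N = 125:

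- 125 × 126 / (12 × 25) = 52.5, and √52.5 = 7.246
- 3.858 × 7.246 = 27.95

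Suppose the other three arms lie wholly beyond both compared arms. The two arms then fill 50 adjacent ranks, and their mean ranks can differ by at most 25. Since 25 < 27.95, the contrast cannot be declared however large the true difference. With 29 per arm the figures are 29 and 30.09. This layout is extreme, but it shows the mechanism. Ranking only within the pair removes it.

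**3. Simulated power for one 2 cm contrast.** Settings: 25 per arm, Kruskal-Wallis required to be significant first, all ten pairwise contrasts adjusted for. Steel-Dwass uses the same Tukey-type adjustment but ranks within each pair, so it isolates the effect of joint ranking.

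| Layout (mean gains, cm) | Errors | Joint-rank Tukey | Steel-Dwass | Holm-Wilcoxon |
|---|---|---|---|---|
| All four active arms 2, control 0 (SD 2.5) | normal | 0.45 | 0.45 | 0.44 |
| | strong skew | 0.79 | 0.77 | 0.78 |
| 4/2/2/2/0, active v placebo laser plus stretching (SD 2.47) | normal | 0.41 | 0.47 | 0.50 |
| | moderate skew | 0.45 | 0.55 | 0.59 |
| | strong skew | 0.66 | 0.78 | 0.83 |
| Other three arms all 2 cm beyond the nearer compared arm (SD 2.5) | normal | 0.25 | 0.45 | 0.51 |
| | strong skew | 0.19 | 0.77 | 0.84 |

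The 4/2/2/2/0 order is active laser plus stretching, placebo laser plus stretching, stretching, laser, control. Separate runs of that layout gave 0.40 v 0.49, 0.45 v 0.59 and 0.65 v 0.84 for joint-rank Tukey v Holm. With the skew in the opposite direction and SD 2.5, strong skew gave 0.62 / 0.77 / 0.82.

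**4. How much of the gap is joint ranking.** Under 4/2/2/2/0, divide (Steel-Dwass − Tukey) by (Holm − Tukey):

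- normal: 0.06 / 0.09 = 67 %
- moderate skew: 0.10 / 0.14 = 71 %
- strong skew: 0.12 / 0.17 = 71 %

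The remaining third or so is Holm's step-down gain.

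**5. False positives.** For two equal arms, the joint-rank test declared a difference in 0.000 to 0.005 of trials. With arms of 29/25/25/20/20 and no true differences, its mean-rank form had a family-wise error of 2.9 to 3.7 %.

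**The case against.** Joint-rank comparison after Kruskal-Wallis is an established procedure that controls family-wise error and uses the overall test's own ranks. The article's wording offers the tests as examples, and a full protocol or SAP may name the variant. In the planning case, with every active arm 2 cm better than control, nothing is lost. All of this stands, and it limits the point to an improvement. It does not remove it, because the article does name a method and a better one is available.

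A reader might also infer several stronger things that the documents do not support:

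- **A parametric test on raw values.** The article labels the test nonparametric, which excludes this.
- **A test that fails with unequal arms.** Drop-out and per-protocol exclusions will probably unbalance the arms, but the mean-rank (Tukey-Kramer) form accepts that. An error of about 10.6 % arises only if someone enters 29 for arms of other sizes, which the article nowhere plans.
- **A loss of up to half.** Half is neither typical nor a ceiling. The loss ranges from nil, through about a fifth against Holm under the trial's hypothesis, to about three quarters in the steepest skewed layout above: (0.77 − 0.19) / 0.77 = 75 %. That layout sits badly with the 2-point advantage over control planned for the treatment groups.
- **The other arms decide the result.** They influence its power. They do not create false positives.
- **The fall from 80 % to about 45 % is due to Tukey.** It comes from adjusting for ten contrasts, and Steel-Dwass and Holm share it.
- **No estimate in cm.** The article plans an Average Gain, the pre-post difference, which for VAS is in cm. What it lacks is an estimate and interval that belong to the rank test itself.

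**Conclusion.** The point holds as a minor one. On its natural reading, the planned non-parametric post hoc test makes the power of a two-arm contrast depend on arms outside it. For the sham-controlled laser contrast, under a layout that fits the trial's hypothesis, this costs about 6 percentage points with normal errors, 10 with moderate skew and 12 with strong skew against Steel-Dwass. Against Holm-adjusted Wilcoxon tests the cost is about 9, 14 and 17 to 19 points. There is essentially no loss if only control differs, and more in steeper layouts. The skewed figures matter most, because data that pass the normality check go to ANOVA.

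The error is one of lost power, not of validity. It applies only to outcomes sent to the Kruskal-Wallis branch. All sizes rest on an SD of about 2.5 cm inferred from the 25 per group, on 25 analysed per arm, and on assumed arm means and error shapes.

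**What to change.** In the Statistical analysis section, replace the non-parametric Tukey test with wording such as: *pairwise Wilcoxon-Mann-Whitney tests, each ranked only within the two arms compared, with Holm adjustment over the ten contrasts, reported with the Hodges-Lehmann difference and 95 % CI in the unit of the outcome.* Steel-Dwass is an acceptable alternative. Either accepts unequal arms, and the VAS estimate can be read directly against the 2 cm used for the sample size.

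The cost is one sentence and up to ten rank-sum tests per affected outcome. Where only one arm differs from the rest, Holm gives up about 1 to 2 percentage points of power (0.45 v 0.44 normal; 0.79 v 0.78 strong skew). The family-wise error of the Holm version stayed at or below 0.047 in all settings tried. The Timeline section places the analysis after the last participant finished, so the choice should be fixed and dated before the outcome data are examined by arm.

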### Participants

One hundred and forty-five men and women aged 50–75 years with symptomatic radiographic knee OA will be recruited from the *Serviço Especializado em Reabilitação* (SER) of Taboao da Serra, Sao Paulo, Brazil. This clinic provides multidisciplinary care, with specialties in orthopaedics, rheumatology, neurology, psychology, physiotherapy, occupational therapy, speech therapy, nursing and social care. The use of this site was authorized by the Secretary of Health of Taboao da Serra and by the General Director of the establishment.

Participants will be eligible if they have (i) radiographic evidence of knee osteoarthritis between 2 and 4 in Kellgren and Lawrence classification [25]; (ii) pain intensity ≥ 3 on a 10 cm Visual Analogue Scale (VAS); and (iii) knee symptoms for at least 3 months.

Participants will be ineligible if they (i) have symptomatic hip osteoarthritis; (ii) have any disease where laser treatment is contraindicated (cancer and uncontrolled diabetes mellitus); (iii) use continuous anti-inflammatory drugs; and (iv) have other concurrent injury/conditions that will affect their ability to participate in the rehabilitation program and/or assessment procedures.

All participants will be informed about the study’s objectives, timeline, and eligibility criteria, then asked to sign an informed consent form if they agree to take part in the study. Participants excluded at this stage will be referred to the physiotherapy sector and followed with the standard of care provided by the service (10 sessions).

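### Groups are compared on unadjusted pre-post gain, by a test that a normality check selects; adjusting for the baseline already collected would be more precise and would fix the analysis in advance

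*Protocol article*

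**What the plan says.** The Statistical analysis section of the protocol article sets the quantity to be compared: "The Average Gain will be calculated for intergroup analysis and will be obtained by the difference between pre and post intervention for each variable". It then sets how the test is chosen: "For adherence to normality, the Kolmogorov-Smirnov test will be conducted". Normal data go to one-way ANOVA and other data to Kruskal-Wallis, each with its own post hoc test. No model in the article has a baseline term.

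The same section adds, for judging clinical importance, a "Relative Gain that corresponds to the gain that the patient obtained after the end of treatment relative to how much they could improve".

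Three other sections bear on the point:
- Assessment procedures: outcomes are measured before treatment starts, so the covariate exists.
- Participants: entry requires a VAS of at least 3 on the 10-cm scale, which cuts off the lower part of the baseline distribution.
- Sample size calculation: the target is stated as "Using a minimal clinically important change of two-point difference between the treatment groups and control group", and "we estimated that 25 participants were needed in each group". No SD and no pre-post correlation are given.

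**The concern.** A raw gain subtracts the whole baseline value, as if the slope of follow-up on baseline were 1. When the slope is lower, the gain remains correlated with baseline. That has two consequences. The gain varies more than a baseline-adjusted outcome, so intervals are wider than they need be. And if one arm happens to start with more pain, part of that difference appears as extra gain.

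The switch is a separate weakness. A preliminary test on the trial's own data decides, outcome by outcome, whether the hypothesis concerns means or ranks. Until the data are in, the primary pain comparison is therefore not settled.

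At stake is precision in a trial planned for 25 analysable participants per arm, and one primary analysis that is fixed in advance.

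**Working it through.** **Inputs.** From Sample size calculation: target difference 2 cm, two-sided 5 % level, 80 % power, 25 per group. From Participants: baseline VAS between 3 and 10. Assumed, because the article does not state it: pre-post correlation r = 0.3, 0.5 or 0.7.

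**The plan's own figure.** The 25 per group cannot be reproduced without an SD. Solving backwards by the normal approximation gives SD = 2 × √(25/2) / (1.960 + 0.842) = 2.52 cm; with the t test it is 2.47 cm. I use 2.47 cm below as a back-solved value, not a stated one.

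**Variance.** Let sx and sy be the baseline and follow-up SDs.
- Gain: sx² + sy² − 2·r·sx·sy
- ANCOVA: sy²(1 − r²)
- The first minus the second is (sx − r·sy)², which is never negative. In large samples the gain can equal ANCOVA but not beat it.

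*Setting A, equal SDs.* The ratio ANCOVA/gain reduces to (1 + r)/2.

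*Setting B, baseline narrowed by the entry rule.* As an illustration, a flat spread over 3 to 10 has SD 7/√12 = 2.02; follow-up SD stays at 2.47. Then sx² + sy² = 4.08 + 6.10 = 10.18 and sx·sy = 4.99. At r = 0.5 the gain variance is 10.18 − 4.99 = 5.19, the ANCOVA variance is 6.10 × 0.75 = 4.58, and the ratio is 0.88.

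**Shift from imbalance.** A baseline difference D moves the gain contrast by (1 − r·sy/sx) × D. One standard error of D with 25 per arm is sx × √(2/25).
- Setting A: 2.47 × 0.283 = 0.70 cm. At r = 0.5 the shift is 0.5 × 0.70 = 0.35 cm, or 0.35/2 = 17.5 % of the target.
- Setting B: 2.02 × 0.283 = 0.57 cm. At r = 0.5 the slope is 0.5 × 2.47/2.02 = 0.61, so the shift is 0.39 × 0.57 = 0.22 cm, or 11 % of the target.

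| r | Variance saved, A | Variance saved, B | One-SE shift, A (cm) | One-SE shift, B (cm) |
|---|---|---|---|---|
| 0.3 | 35 % | 23 % | 0.49 | 0.36 |
| 0.5 | 25 % | 12 % | 0.35 | 0.22 |
| 0.7 | 15 % | 3 % | 0.21 | 0.08 |

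**Check by simulation.** Two arms of 25, SD 2.5 before truncation, baseline cut to 3–10, follow-up clipped to 0–10, true shift 2 cm, 4000 runs; r is the correlation before truncation. Power for gain against ANCOVA was 70 % against 81 % at r = 0.3, 82 % against 88 % at 0.5, and 96 % against 97 % at 0.7. With no true effect, both methods rejected in 4.6 to 5.0 % of runs.

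**The case against.** The best defence is that nothing here is invalid. Arms are randomised, so the gain contrast is unbiased over randomisations, and the simulation shows the type I error is kept. The VAS entry rule applies to all five arms, so regression to the mean does not by itself favour any of them. All of this stands. A reader might infer that the planned test is biased; the article does not support that. The imbalance effect is conditional on the allocation that happens to occur. (This concerns arms compared as randomised; the per-protocol principle in the Abstract is a separate matter.)

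Second, the loss may be small. In setting B at r = 0.7 it is 3 %, and it vanishes where r·sy = sx, at r = 2.02/2.47 = 0.82. This also stands, and it is why only a range can be given.

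Third, the switching rule is itself written down in advance, and Average Gain is in centimetres for VAS whichever test is run. So it would be wrong to say that the rank route leaves no centimetre figure. What remains is that the hypothesis tested still depends on the data, and that a rank test does not test that mean difference.

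Fourth, Relative Gain. It is tempting to say that it distorts the comparison of arms, reverses their ranking or drops patients with a zero denominator. The article ties it to clinical importance and assigns Average Gain to the intergroup analysis. It states no exclusion rule, and nothing shows a reversal.

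None of this answers the main point. The article positively fixes an unadjusted quantity and a data-chosen test, so this is not a detail left to a fuller document.

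**Conclusion.** The point holds as one of efficiency and prespecification, not of validity. The planned comparison gives up precision that the collected baseline data could supply. Within a given randomisation it carries part of any chance baseline difference, and it does not settle in advance whether means or ranks are compared for pain.

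Over the settings examined, ANCOVA saves between about 3 % and 35 % of the variance. In interval width that is a reduction of between 1 − √0.97, about 1 to 2 %, and 1 − √0.65, about 19 %. At r = 0.5 a one-SE imbalance moves the estimate by about 0.2 to 0.35 cm against 2 cm.

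These figures rest on an assumed r, on an SD back-solved from 25 per group, and on how far the entry rule narrows the baseline spread. The larger figures need equal SDs, which sit badly with a baseline cut at 3, so they should be read as the upper end. The direction does not depend on these choices: apart from the one degree of freedom spent on the covariate, adjustment does not lose precision to the gain score.

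**What to change.** Make a dated amendment before any group comparison is seen:
- For each continuous outcome, the primary analysis is an ANCOVA of the end-of-treatment value on arm (five levels) with that outcome's baseline value as covariate.
- Report adjusted mean differences with 95 % confidence intervals. For VAS, set them against the plan's own 2-cm between-group difference.
- Drop the Kolmogorov-Smirnov switch. If residuals are skewed, use robust or bootstrap standard errors.
- Keep the gain and rank comparisons as sensitivity analyses.
- Relative Gain may stay as a descriptive measure, but clinical importance should be judged on the adjusted difference. No responder cut-off is needed: the 2 cm is stated as a difference between groups, not as a change within a patient.

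The cost is analysis wording and an amendment; no new data are required. Timing matters, because the Timeline section says that all participants had finished by December 2014 while the analysis was still to be completed. If group results have already been seen, the ANCOVA should be reported next to the planned analysis and labelled as added afterwards.
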